#### Qualitative Interview (Parents)

Parents will evaluate the learnability and usability of their VR experience. Questions reflect on how their experience with VR was, what they believe is the added value of VR to the therapy, and whether VR helped to strengthen and comprehend parenting skills at a faster pace. They will be asked qualitative questions about their VR experience during the posttreatment and follow-up assessments. In addition, questions surrounding whether the VR simulation is compatible with their manners of speaking to their children will also be asked.

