Secondary objectives are the effects that we expect because of the overall amelioration of positive parenting skills that cause both parental stress and child disruptive behavior to diminish. Therefore, we expect that the total number of PCIT sessions will diminish and that the overall completion of treatment will increase. In addition, family dynamics and competencies will be secondarily measured, meaning that we will be able to evaluate parental compliance in the use of VR and evaluate potential risk factors for dropout. We believe that parents choosing to use VR will show higher levels of compliance as they want to use an additional tool to learn the skills. Secondary objectives also include positive VR experiences and general therapy satisfaction. Furthermore, we expect that PCIT-VR will secondarily lead to a better quality of parent-child relationships. We expect that the effects of PCIT-VR are further maintained and engrained in the long term because of the additional skill training provided by the VR scenarios.

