The multiple baseline SCED in this study is set up as shown in Figure 1. First, informed consent will be signed after families have received verbal and written information about the study. Second, participants will be dually randomized (by an external party) to determine their baseline period (4, 5, or 6 weeks of baseline measurements; phase A) and the addition of their VR element (VR at the start of CDI and after 3 or 6 sessions of CDI; phase B). After randomization, participants will start with phase A—the baseline period. Parents will electronically fill out the questionnaires weekly regarding child disruptive behaviors and parental stress using the ECBI and the short version of the OBVL. At the end of phase A, a pretreatment assessment will be performed. In this assessment, parents will be required to electronically fill out more questionnaires regarding both child and parental factors (Figure 1; see the *Assessment Instruments* section). In addition, the researcher will also make a video recording of the parent and child playing in 3 play situations (child-led play [CLP], parent-led play [PLP], and clean up [CU]), which will consequently be coded using the Dyadic Parent-Child Interaction Coding System (DPICS) [52]. Following this, in phase B, the intervention phase starts. Depending on their random allocation, families will start off with PCIT with or without the VR element. Once again, they will electronically fill out the ECBI and OBVL-*kort* (OBVL-K) weekly, and they will also register their homework completion and (if applicable) their VR completion sheets. During the PCIT sessions, PCIT therapists will register the parental progress weekly by coding 5 minutes of playtime with the DPICS. Once families reach CDI completion, they will move on to phase C, which is the parent-directed interaction (PDI) phase of PCIT. Measurements in phase C are identical to those in phase B. After treatment completion, a posttreatment assessment will be performed, which will be identical to the pretreatment assessment. Phase D is the follow-up assessment, which takes place 6 months after treatment completion. The assessment is also identical to the pre- and posttreatment assessments (Figure 2; 10 CDI sessions and 6 PDI sessions are used as a random example).

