### Treatment

PCIT focuses on changing dysfunctional parent-child interactions in 2 phases and teaches authoritative parenting [17], which implies firm control, warmth to the parent-child relationship, and a balance between discipline and stimulating independence [53]. Therapists coach parents from behind a 1-way screen through an earpiece [17]. In the first phase of PCIT, which is the CDI phase, emphasis is placed on building up the quality of the parent-child relationship and increasing positive parenting skills. In addition, in this phase, children begin to build the ability to regulate their behavior [15]. This first phase lays the foundation for effective behavior change. In the CDI phase, parents follow their child’s lead in playing and are coached on using positive parenting skills, specifically, praise, reflective statements, behavioral descriptions, imitation, and enthusiasm [17]. The number of CDI sessions is dependent on the parents meeting the skill criteria (10 behavioral descriptions; 10 reflective statements; 10 labeled praises; and <3 questions, commands, or negative verbalizations during a 5-minute observation period).

However, the CDI phase alone is typically insufficient for children with disruptive behavior to return to displaying normal behavior [54]. After meeting the CDI skill criteria, the second phase of PCIT, which is the PDI, starts. The goal of the PDI phase is to further enhance the parents’ positive parenting skills to set consistent, predictable, and age-appropriate boundaries for their children [17]. In the PDI phase, parents are coached on using clear commands and how to apply consequences for compliance (praise) and noncompliance (timeout). In addition, they are taught and encouraged to keep using the positive parenting skills from the first phase. Once parents demonstrate achievement of skill criteria of both CDI and PDI skills, and their children’s behaviors according to the raw score on the ECBI Intensity Scale is <114, the treatment is completed, as standard protocol dictates [17].

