### Therapy Evaluation

#### Therapy Attitude Inventory

The Therapy Attitude Inventory [60] is a 10-item scale that evaluates parental satisfaction with the treatment. This questionnaire will be filled out once by the parents at the end of the treatment. Although information regarding the reliability and validity of the Dutch translation of the TAI is missing, the original version has shown adequate psychometric properties [61].

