#### Qualitative Interview (Parents)

A qualitative interview after treatment and follow-up assessments will allow parents to share their experiences with regard to the new form of PCIT-VR and the extent to which this therapy strengthened their competences and made them see their own abilities.

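### On the stated schedule, VR experience and therapy satisfaction are reported essentially by families that complete treatment, so these two secondary results are likely to be favourably selected

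*Protocol article*

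**What the plan says.** The Aims section of the protocol article states: "Secondary objectives also include positive VR experiences and general therapy satisfaction". Three parent measures serve these objectives:

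- **VR interview** (VR Evaluation, Qualitative Interview): "They will be asked qualitative questions about their VR experience during the posttreatment and follow-up assessments".
- **Therapy Attitude Inventory** (Therapy Evaluation), a 10-item satisfaction scale: "This questionnaire will be filled out once by the parents at the end of the treatment".
- **Therapy interview** (Therapy Evaluation, Qualitative Interview): "A qualitative interview after treatment and follow-up assessments will allow parents to share their experiences".

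Study Design fixes the two assessment points: "After treatment completion, a posttreatment assessment will be performed, which will be identical to the pretreatment assessment", and "Phase D is the follow-up assessment, which takes place 6 months after treatment completion". The Treatment section defines completion by performance rather than by calendar time: "Once parents demonstrate achievement of skill criteria of both CDI and PDI skills, and their children’s behaviors according to the raw score on the ECBI". The threshold set there is a raw Intensity score below 114. The article describes no parent interview or satisfaction form for a family that stops before that point.

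**The concern.** Completion is itself a success criterion. The VR interview asks whether VR helped parents understand the skills faster, and on this schedule the question goes to parents who have already mastered them. The Introduction says that parents drop out because they cannot fully understand the skills and carry them over to the home. That is the difficulty VR is meant to ease. The Introduction also cites a study in which completers had fewer child behavior problems and less parental stress at follow-up than dropouts. By the article's own reasoning, the families not asked differ from those asked, and in a way that bears on the question.

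At stake is how two secondary results are read. The abstract's Conclusions name routine use of VR within PCIT as the eventual goal, and satisfaction or usability findings drawn from completers would be an incomplete basis for that.

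**Working it through.** **Inputs from the protocol article**

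- Planned families: 15 (Participants).
- Replicated cases needed: 9 (Participants).
- Attrition used for planning: 40% (Participants).
- Attrition given in the Introduction for the Dutch study: 52%.
- Attrition range for standard PCIT: 34% to 77% (Participants).
- VR start: at the beginning of CDI, or after 3 or 6 CDI sessions (Study Design).

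**Step 1: reproduce the plan's own figure.** 9 / (1 − 0.40) = 15. This matches exactly, so 15 is read as the number enrolled and 9 as the expected number of completers. The inflation protects the number of completers. It does nothing about who they are.

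**Step 2: families asked under the stated schedule.** Expected completers = 15 × (1 − d); expected families not asked = 15 × d.

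| Attrition d | Asked | Not asked |
|---|---|---|
| 34% | 9.9 | 5.1 |
| 40% (planning figure) | 9.0 | 6.0 |
| 52% (Introduction) | 7.2 | 7.8 |
| 77% | 3.45 | 11.55 |

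**Step 3: adjust for VR experience.** A family that stops before its VR start has no VR experience to report, so the not-asked column applies in full to satisfaction and is an upper figure for VR experience. The allocation ratio is not stated. Assume equal thirds, dropout unrelated to allocation, and dropout only after CDI has begun. At 40%, 6 / 3 = 2 of the lost families had VR from the start, and the other 4 count only if they stayed to session 3 or 6. The loss for VR experience is then between 2 and 6 families.

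**Step 4: how far a summary could move (illustration only).** The article gives no satisfaction rates and does not say that a percentage will be reported. Assume that 90% of completers and 30% to 70% of dropouts are satisfied:

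- d = 40%: 0.60 × 0.90 + 0.40 × (0.30 to 0.70) = 0.66 to 0.82.
- d = 52%: 0.48 × 0.90 + 0.52 × (0.30 to 0.70) = 0.59 to 0.80.

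The observed figure would be 90% in both cases. Without any assumption about dropouts: if every completer is satisfied, the value over all families lies between 60% and 100% at d = 40%, and between 48% and 100% at d = 52%.

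**The case against.** The strongest reply has four parts.

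*Families that stop are not invisible.* Log-in analytics and weekly VR completion sheets run until a family leaves. The Discussion promises close contact with parents and registration of individual obstacles as they arise. Therapists are interviewed about the benefits and obstacles of PCIT-VR, and nothing limits this to completers. A reader might infer that VR as a reason for stopping could never come to light; the article does not support that. What stands is that logs measure use rather than experience, that obstacle registration has no stated instrument or schedule, and that therapists' views are not parents' views.

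*Nothing excludes families that stop.* The inventory is timed to the end of treatment and the therapy interview to after treatment; neither text says completion, and a full protocol that is not shown may contain an exit contact. This is fair. The point therefore rests on the stated timing, which is firmest for the VR interview, and should not be read as an exclusion rule.

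*Timing within treatment is not a fault.* Because the scenarios depict CDI skills, a reader might infer that the interview relies on recall from weeks earlier, after the whole PDI phase. The article does not say that VR stops with CDI. Phase C measurements are the same as those in phase B, which include the VR sheets, and the sheets are required weekly once VR is received. There is no case here for an extra interview at the end of CDI.

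*These are descriptive secondary objectives.* This is correct. The primary DPICS outcome is coded weekly in sessions while families are in treatment, and this point does not touch that coding. That limits the weight of the point but does not remove it.

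**Conclusion.** The concern holds in a limited form. Followed as written, the schedule has VR experience and therapy satisfaction answered essentially by completers: about 9 of 15 families at 40% attrition and about 7 at 52%. For satisfaction, about 6 to 8 families are not asked; for VR experience that count is an upper figure. Favourable selection is likely, given the performance-based definition of completion and the article's own account of why parents leave. Its size cannot be derived from the document, and the percentages in the working are illustration only.

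The conclusion assumes that 15 is the number enrolled, that attrition is near the article's figures, and that no exit contact exists in a fuller document. The change is worth making because it is cheap.

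**What to change.** Amend the two parent-interview sections and the Therapy Attitude Inventory section so that the existing instruments are given at treatment completion or at withdrawal from treatment, whichever comes first:

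- the VR interview, for families that had received VR;
- the 10-item Therapy Attitude Inventory, for all families;
- the therapy interview, with its timing brought into line in the same contact.

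The follow-up interviews stay as planned. Report completers and non-completers separately, with the number not reached in each group. If a fuller protocol already provides an exit contact, state it in these sections.

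The cost is one short contact with about 6 to 8 families. It needs no new instrument. Some families that stop will refuse, so the selection will be reduced and made visible rather than removed.

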### Psychological Functioning (Child)

#### Questionnaire Background Information

This questionnaire contains questions with regards to background information about the child and his or her family. Questions concerning sex, age, ethnicity, family composition, parental work situation, and education level are included. This questionnaire will be filled out at the pretreatment assessment. If necessary, their treatment file can be consulted for supplementary information.

#### Child Behavior Questionnaire: ECBI

The ECBI [44] is a questionnaire containing 36 items, which is filled out by parents and addresses child behavioral problems for children aged between 2 and 16 years. The ECBI is a part of the standard protocol of PCIT. The scale has good psychometric properties. Both the frequency of problem behavior (Intensity scale; 7-point scale from 1 [never] to 7 [always]) and the extent to which parents experience the behavior as problematic at that moment in time (Problem scale; yes or no) will be measured. Parents will complete the questionnaire at all assessment points.

#### Kind en Jeugd Trauma Screener

The Dutch translation of the Child and Adolescent Trauma Screen, which is the Kind en Jeugd Trauma Screener [55] screens for exposure to traumatic events and posttraumatic stress disorder symptoms. It is based on the Diagnostic and Statistical Manual of Mental Disorders, Fifth Edition, and contains 16 items in addition to 5 dichotomous questions about how symptoms limit their daily functioning. The psychometric values of the Dutch translation are currently being researched; however, according to the English, German, and Norwegian versions of the screening questionnaire, it is valid and reliable [55]. Parents will complete this questionnaire at the pretreatment and posttreatment assessments.

#### Child Abuse Potential Inventory

The Child Abuse Potential Inventory [56] is a questionnaire filled out by parents, which measures the chances that parents (physically) abuse their child (aged between 0 and 18 years). All 34 items include a statement with which parents could either *agree* or *disagree*. The psychometric properties of the Dutch translation have been shown to be reliable and valid [57]. This study will use the short version. Parents will fill out this questionnaire at the pretreatment and posttreatment assessments.

### Family Dynamics and Competences

#### Dutch Parenting Stress Questionnaire: OBVL

The OBVL [45] is a Dutch questionnaire with 34 questions that address five aspects of parenting stress: problems in the parent-child relationship, problems in parenting, depressed moods, role restriction, and health complaints. The total score on parenting burden can be calculated. The OBVL has high reliability, and norms have been measured for different age groups, indicating that its psychometric properties are good. Parents will complete this questionnaire during pre- and posttreatment and follow-up assessments.

#### Dutch Parenting Stress Questionnaire, Shortened Version: OBVL-K

The OBVL-K [45] is a shortened version of the OBVL. It comprises 10 questions that together provide a total score on the burden of parenting. This questionnaire has high reliability, and norms have been measured for different age groups, indicating that its psychometric properties are good. Parents will complete this questionnaire weekly to obtain a general overview of their parental burden throughout the process.

#### Adult Self-report

The Adult Self-Report [58] is a self-report measure of competencies and emotional and behavioral problems for adults and is based on the Diagnostic and Statistical Manual of Mental Disorders. The questionnaire is split into 2 sections, one concerning competencies and work and the second concerning emotional and behavioral problems. The English version has been shown to be reliable and has good validity. The psychometric properties of the Dutch version are yet to be evaluated. The parents will complete this self-report during pre- and posttreatment assessments.

#### Attachment Insecurity Screening Inventory

The Attachment Insecurity Screening Inventory (AISI) [59] is a questionnaire that measures attachment problems. The questionnaire contains 20 items that together form total attachment but are divided into three subcategories: avoidant, ambivalent/resistant, and disorganized attachment. The AISI 2-5 was found to be valid and reliable according to recent research [59]. The AISI 6-12 is practically identical to the AISI 2-5 but has not been tested for validity and reliability. Nonetheless, studies have shown that the AISI is a promising instrument for measuring attachment insecurity in young children [59]. The AISI will be filled out by parents during the pre- and posttreatment assessments.

### Therapy Evaluation

#### Therapy Attitude Inventory

The Therapy Attitude Inventory [60] is a 10-item scale that evaluates parental satisfaction with the treatment. This questionnaire will be filled out once by the parents at the end of the treatment. Although information regarding the reliability and validity of the Dutch translation of the TAI is missing, the original version has shown adequate psychometric properties [61].

#### Qualitative Interview (Parents)

A qualitative interview after treatment and follow-up assessments will allow parents to share their experiences with regard to the new form of PCIT-VR and the extent to which this therapy strengthened their competences and made them see their own abilities.

#### Qualitative Interview (Therapists)

Therapists will also be asked about their experiences and vision of the effectiveness of PCIT and their vision of the added value of VR to the therapy at the end of the data collection period. They will be asked what factors contribute to effectiveness, including factors such as their relationship with parents or specific characteristics. Through this interview, the different benefits and obstacles of PCIT-VR can be brought to light through the eye of the therapist.

### Statistical Analysis

Data analysis will take place in consultation with a statistics expert from the Clinical Research Unit department of the Amsterdam University Medical Center (UMC). Data analysis will include the following:

Primarily, the added value of VR to PCIT will be evaluated through analyses.SCED analyses will be conducted with the Shiny app.Repeated measures analyses will be conducted.Graphical analyses will be conducted to render the change over time.

Qualitative information from the interviews will be summarized into a complete picture of the experiences of both parents and therapists. This will include their experiences with PCIT-VR, the VR component in particular, and how the therapy helped them gain insight into strengthening their competencies. All qualitative information will be analyzed using structured qualitative interview software, for which we will also seek consultation with an expert.

### Confidentiality of Data

The data for this study will be collected by researchers from the Department of Child and Adolescent Psychiatry at the Amsterdam UMC. The Clinical Research Unit of the Amsterdam UMC provides support for the data analysis of this study. All data will be stored in coded form by assigning personal numbers to each family and registering all information using that number. This ensures that only authorized people can trace which file belongs to which family. All study results will be published anonymously.

### Ethics Approval

This study was approved by the medical ethics committee of the Academic Medical Center of Amsterdam, Netherlands (2020_143). Informed consent for participation in the study will be obtained; among other permissions, parents will also provide permission for video recording of their child. The way informed consent will be obtained for the study was approved by the medical ethics committee of the Academic Medical Center of Amsterdam, the Netherlands (2020_143).

## Results

As of February 2021, 6 families have been enrolled in the study at the time of submission. Data collection is projected to be completed in 2023. Both quantitative and qualitative results are planned to be published in peer-reviewed journals, as well as being presented at national and international conferences. The study is registered at the medical ethics committee of the Academic Medical Center of Amsterdam, the Netherlands (2020_143/NL74210.018.20) and the Netherlands Trial Register NL9580.

## Discussion

### Principal Findings

This study is the first to implement a VR element that functions as additional *skill training* to magnify the scope of PCIT through practice. Similar to standard PCIT, the intervention is centered around parent-child play sessions, where parents receive live feedback and support from a therapist. The additional VR element provides parents with the opportunity to practice positive parenting skills in the comfort of their own homes without their child present while still receiving feedback. This allows them to further engrain the skills alongside the therapy sessions and special time. Therefore, we expect that the implementation of VR will lead to faster achievement of meeting the skill criteria. Furthermore, this study expects that parental stress, child disruptive behavior, dropout rates, and the number of necessary therapy sessions will diminish as a secondary effect of the additional VR element.

Currently, the technology behind the VR element is being developed in parallel with the study, meaning that the development of VR is fluid. This is an asset as it means that the application can be adapted if any technical problems arise. A potential problem that could be encountered and should be resolved as soon as possible is the functioning of the web-based VR application on different smartphones. The application, the videos, and the technology that underlies this must be designed in such a way that it is supported by all types of smartphones and their software versions. To find the right fit for smartphones, testing must be performed on multiple devices before offering them to parents. To minimize the potential obstacles and rather use them as learning points, close contact will be kept with both technical support and parents. Parental feedback will be processed as soon as possible by the technical support, and adaptations will be made where and when necessary. Fortunately, SCEDs lend themselves well to this flexibility, as each individual trajectory has different phases (baseline and treatment phase), thus enabling comparison between phases and even between measurement points. This means that the VR obstacles faced by one family may differ from those of another family. Therefore, this study offers an opportunity to flexibly implement VR and register individual obstacles as they occur, both qualitatively and quantitatively.

The implementation of VR later on in CDI sessions could potentially limit its effect on improving positive parenting skills, as the rate of skill growth from session to session usually gradually declines as families get closer to meeting skill criteria. Nonetheless, the strength of SCEDs designed with phases, randomization, and the opportunity to replicate means that it allows for the comparison of an individual in different phases of treatment. Thus, it allows us to follow progression while also being able to compare the treatment effects of multiple individuals at different times. As analyses are conducted both visually and statistically, a clear overview can be provided for both individual and group treatment effects. This means that both individual and group outcomes can indicate whether the timing of VR implementation affects the effect on acquired positive parenting skills. However, SCEDs also have some potential limitations. For example, there is a risk of type I errors because of the potential violation of distributional assumptions and the presence of serial dependencies. In addition, it is possible that there is an unexpected data trend because of maturation effects (eg, gradual bettering of VR analytics because of habituation to scenarios). With the right statistical support, these pitfalls can potentially be mitigated, which is something the research group intends to do.

